## Materials and methods

### Study design

The SALUS study is a multicenter, two-arm parallel group, open non-inferiority, randomized controlled trial with an economic analysis alongside.

This non-inferiority design was chosen to establish that outpatient monitoring of IOP with self-tonometry is not less effective than standard care with hospitalized monitoring of IOP. The trial will be conducted in hospitals and patients’ homes in the district of Westphalia-Lippe, Germany. Each participant will be followed for 12 months from the start of the trial, with regular follow-up every 3 months by local ophthalmologists (see Fig. 1).

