### Randomization

After informed consent, patients will be randomized 1:1 into the IG and CG. The randomization will be generated automatically by the ECF after the local ophthalmologist has submitted the patient’s master data (year of birth, sex, and three digits of the zip code) and eligibility criteria in a web-based form. The underlying randomization sequence will be known only to the developers of the ECF (Fraunhofer Institute for Applied Information Technology FIT) who will act independently of the personnel analyzing (Bielefeld University) and conducting (University of Muenster Medical Center) the study. This sequence will be concealed from all study staff so that it cannot be manipulated by physicians, clinical staff, or the patients themselves.

Participants will receive a study identification number after randomization and their assignment to one study group. Owing to the nature of the intervention, it will not be possible to blind either the patients, the personnel conducting the study or the healthcare providers. The independent evaluators of the study will be blinded during the study by being provided solely with a pseudonymized data set for data analysis.

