### Sample size

The sample size was determined using the license-free software “R” (R v. 3.6.3, Rstudio v. 1.2.5042). The estimation of sample size and power analysis is based on the primary endpoint “exceeding patient-specific target pressure”. As null hypothesis, it is assumed that the proportion of pressure peaks in IG is smaller than the proportion in CG (i.e., non-inferiority).

Based on clinical experience, a margin of 20% is assumed for detection of IOP fluctuations and peak values in both groups. A non-inferiority margin of *δ* = 0.05 is acceptable, meaning the proportion of pressure peaks in self-tonometry should fall below the proportion in 24 h IOP by more than 5% to be taken as a statistically significant difference [34, 35]. With regard to the probability of type I and II errors, significance levels will be set at *α* = 0.05 and *β* = 0.2, respectively, i.e., a power of (1 − *β*) = 0.8. This results in a total of 1584 patients (792 per group). After adjusting for a drop-out rate of 20%, a final sample size of 1980 patients (990 per group) will be required for this trial (see Fig. 2).

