Data will be analyzed on the intention to treat principle (ITT). Thus, all participants who have given their informed consent will be included in the evaluation. More precisely, all patients of the IG and CG will need to be informed about the use of their data, and their willingness to participate must be ascertained and documented. Allocation to IG and CG as well as randomization will be conducted independently after recruitment of the study participants to ensure structural equality of the data between the two groups. To maintain this structural equality for data analysis, all participants will be evaluated according to the ITT principle as members of the treatment group to which they were randomized, whether or not the study participants used the allocated outpatient or inpatient method of measurement. Further, the potential amount and pattern of missing data will be defined, and if required, appropriate methods such as sensitivity analysis will be applied. This will allow accurate analysis of the assumptions and the effectiveness of self-tonometry in this study [38–40]. All models implemented will provide information on potential treatment effects and will be presented as a 95% confidence interval.

Following the recommendation of the German Institute for Quality and Efficiency in Health Care (IQWiG), the cost-minimization analysis will be carried out from the perspective of statutory health insurance and will, if applicable, be supplemented by analysis from a patient/societal perspective [41]. The economic analysis will conform to the principles of good secondary data analysis, the recommendations of the memorandum “Methods for Health Services Research,” and the standards of the German Evaluation Society [42–44].

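### Non-inferiority rests on intention-to-treat alone, with the method actually used disregarded; any switching between methods would favour the claim, by an amount the protocol does not let us know

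*Protocol article*

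**What the plan says.** The Study design section describes a "multicenter, two-arm parallel group, open non-inferiority, randomized controlled trial", and the Randomization section says that "patients will be randomized 1:1 into the IG and CG". The Sample size section sets the planning values: "a margin of 20% is assumed for detection of IOP fluctuations and peak values in both groups", "A non-inferiority margin of *δ* = 0.05 is acceptable" and "significance levels will be set at *α* = 0.05 and *β* = 0.2". It arrives at 792 evaluable patients per group, or 990 per group after a 20% drop-out allowance.

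The Statistical analyses section adopts ITT and evaluates patients in the group to which they were randomised, "whether or not the study participants used the allocated outpatient or inpatient method of measurement". Its stated reason is to preserve the comparability of the arms. No per-protocol or as-measured set appears anywhere in the article. Sensitivity analysis is mentioned once, for missing data, and only if needed. Model results are to be shown with 95% confidence intervals.

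The Primary endpoint section shows that the outcome comes from the measurement itself. Intervention patients self-measure six times a day for seven days; control patients are measured by staff at the same times of day over at least 24 hours.

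**The concern.** In a superiority trial, disregarding non-adherence is usually cautious, because dilution pulls the estimate towards no difference. In a non-inferiority trial, no difference is the result the sponsor hopes for, so the same dilution works in favour of the claim when the new method is truly worse.

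The effect is unusually direct here. The endpoint is what the tonometry finds, so an intervention patient measured in hospital supplies an inpatient result that is counted as a self-tonometry result.

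Some switching is conceivable. The trial is open, every patient is judged to need inpatient monitoring and has agreed to admission (Table 1, inclusion criteria II and V), and device training comes after randomisation (Intervention section). The ITT rule itself provides for patients who did not use the allocated method.

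At stake is a conclusion that self-tonometry detects peaks acceptably well when part of that detection was done in hospital. The planned cost-minimisation analysis would inherit the error, since it presumes comparable effectiveness.

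**Working it through.** **Inputs from the Sample size section.** Detection 20% in both arms; margin 0.05; α = 0.05; power 0.80; 792 per group evaluable; 990 per group enrolled.

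**Assumed, because the article gives no figure.** The fraction c of the intervention group measured as inpatients and the fraction d of the control group measured by self-tonometry. Switching is taken to be unrelated to a patient's chance of having a peak.

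**Step 1: reproduce the stated size.** n = (z₀.₉₅ + z₀.₈₀)² × 2 × 0.20 × 0.80 / 0.05² = (1.645 + 0.842)² × 0.32 / 0.0025 ≈ 791.4, rounded up to 792 per group, or 1584 in all. Dividing by 0.80 gives 1980. All three figures match. One-sided 0.025 would need 1005 per group, so the plan was sized at one-sided 0.05. A two-sided 95% interval corresponds to one-sided 0.025, so both levels are shown below.

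**Step 2: place the truth on the margin.** Inpatient detection 20%, self-tonometry 15%. The ITT proportions become

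- p_IG = 0.15(1 − c) + 0.20c
- p_CG = 0.20(1 − d) + 0.15d

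and the ITT shortfall is 0.05 × (1 − c − d).

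**Step 3: probability of declaring non-inferiority.** P = Φ[(0.05 + p_IG − p_CG)/SE − z], with SE = √{[p_IG(1 − p_IG) + p_CG(1 − p_CG)]/n}.

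Worked case, c = 0.10, d = 0, n = 792: p_IG = 0.155; SE = √[(0.130975 + 0.16)/792] = 0.01917; 0.005/0.01917 = 0.261; Φ(0.261 − 1.645) = 0.083.

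**Results, 792 per arm:**

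| IG switching | CG switching | ITT shortfall (points) | One-sided 0.05 | Lower limit of two-sided 95% CI |
|---|---|---|---|---|
| 0 | 0 | 5.00 | 5.0% | 2.5% |
| 5% | 0 | 4.75 | 6.5% | 3.4% |
| 10% | 0 | 4.50 | 8.3% | 4.5% |
| 20% | 0 | 4.00 | 13.0% | 7.5% |
| 10% | 10% | 4.00 | 13.1% | 7.6% |

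Simulation with 400,000 runs per scenario agrees at one-sided 0.05: 8.4% at 10% intervention-group switching, 13.1% at 20%, and 13.2% with 10% in both arms. If all 990 per arm were evaluable, one-sided 0.05 would give 8.8% at 10% intervention-group switching and 14.3% at 20%.

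**The case against.** The strongest objection is that the switching premise has no figure behind it. Exclusion criterion III removes patients whose conditions would prevent independent self-measurement. The article describes no route by which an intervention patient is measured as an inpatient instead, and it issues the device only to the intervention group. Agreement to admission is needed because anyone may be allocated to control; it does not show that patients will switch. This stands. The rates above are scenarios, and with no switching there is no inflation.

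Second, a condensed article may leave further analysis sets to a plan that is not shown, and keeping patients as randomised is simply what ITT means. This stands in part. A reader might infer that a per-protocol analysis has been ruled out; the article does not say so. But it is not silent either: it states the analysis basis for the non-inferiority comparison, expressly sets aside the method used, and presents this as sufficient to assess self-tonometry.

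Third, a patient who fails to self-measure may have missing data rather than an inpatient profile. That is a separate problem. Counting such patients as having no peak, mainly in the intervention group, would work against non-inferiority; doing so equally in both arms would favour it.

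Fourth, a per-protocol set is not a clean remedy. It drops the patients who could not use the device, may flatter self-tonometry, and loses the protection of randomisation. This stands. It is why the set should accompany ITT rather than replace it.

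A reader might also take the sentence "Thus, all participants who have given their informed consent will be included in the evaluation" to mean that the analysis set is defined by consent rather than by randomisation. The same paragraph goes on to analyse patients in the group to which they were randomised, so the text does not support that reading.

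**Conclusion.** The point holds in a limited form. The article gives ITT as the sole stated basis for a non-inferiority claim, on an endpoint generated by the measurement method, and provides no analysis that would show whether switching had carried the result. The direction is certain when self-tonometry truly detects fewer peaks: any switching raises the chance of a false claim.

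The size is not known. Under the assumptions above, 10% switching in the intervention group raises a nominal 5% to 8.3%, and 20% raises it to 13.0%. With a 95% interval as the criterion, a nominal 2.5% becomes 4.5% and 7.5%; at 10% switching it is still below the one-sided 5% to which the trial was sized.

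It would be tempting to say that the trial's false-positive rate is 13% or 14%. The documents do not support that, because they give no switching rate, and the 14% also requires all 990 per arm to be evaluable. This is something the sponsor should fix, not a flaw that undermines the trial.

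**What to change.** - Keep ITT, worded plainly as all randomised patients in their randomised arm.
- Prespecify a per-protocol analysis (measured by the allocated method, with an evaluable pressure profile at T1) of the same difference in proportions against the same −0.05 margin.
- Report, by arm, how many patients were measured by the other method and how many did not use the allocated method at all.
- Claim non-inferiority only if the two analyses lead to the same conclusion, and acknowledge in the plan that the per-protocol set is open to selection because it excludes patients who could not use the device.
- If the unseen analysis plan already does this, add a sentence to the protocol saying so.

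The cost is one more analysis, which needs only a record of the method each patient used and the pressure profile, a somewhat stricter success criterion, and slightly lower power in the smaller set. The 20% allowance leaves 792 per arm in the per-protocol set only if drop-outs and patients not measured as allocated together stay within 20%.

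### The 792 per group assumes a one-sided 5% test, but the only stated interval is 95%; judged on a two-sided 95% CI, power would be about 70% to 79%, not 80%

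*Protocol article*

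**What the plan says.** The sample size section of the protocol article sets the error rates: "significance levels will be set at *α* = 0.05 and *β* = 0.2, respectively", "i.e., a power of (1 − *β*) = 0.8". The expected proportion is put this way: "a margin of 20% is assumed for detection of IOP fluctuations and peak values in both groups". The word margin there can only mean the anticipated rate in each arm, because the margin proper follows: "A non-inferiority margin of *δ* = 0.05 is acceptable". The conclusion is "This results in a total of 1584 patients (792 per group"), raised to 990 per group for 20% drop-out. Allocation is equal: "patients will be randomized 1:1 into the IG and CG" (Randomization).

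The section does not say whether alpha is one- or two-sided. Its hypothesis is directional: "it is assumed that the proportion of pressure peaks in IG is smaller than the proportion in CG (i.e., non-inferiority").

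The statistical analyses section names one interval for the whole article: "All models implemented will provide information on potential treatment effects and will be presented as a 95% confidence interval". No 90% interval, one-sided bound or other rule for declaring non-inferiority appears.

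**The concern.** In a non-inferiority trial the conclusion is usually read from one confidence limit compared with the margin. The lower limit of a conventional two-sided 95% interval is a one-sided 2.5% test. The lower limit of a two-sided 90% interval is a one-sided 5% test. The sample size turns out to rest on the second, while the only interval stated is, on its ordinary reading, the first.

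Other wording does not settle the matter. The introduction states the primary hypothesis as the absence of a significant difference, and the sample size section explains the margin in terms of a significant difference. Both are phrases of a difference test, for which 5% two-sided is the usual reading.

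The choice could decide the primary conclusion, since some results would pass at one level and fail at the other. If the 95% interval decides, the stated power is not attained. If a 90% interval decides, the one-sided error rate is 5%, twice the 2.5% that goes with the 95% interval.

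**Working it through.** **Inputs, all from the article.** Proportion with peaks 0.20 in each arm (true difference 0), margin 0.05, power 0.80, alpha 0.05, drop-out 20% (Sample size); 1:1 allocation (Randomization); 95% interval (Statistical analyses).

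**Step 1: reproduce the plan's figure.** For non-inferiority on the risk difference,

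n per arm = (z₁₋α + z₀.₈)² × 2 × 0.2 × 0.8 / 0.05² = (z₁₋α + 0.8416)² × 128.

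- One-sided 5%: (1.6449 + 0.8416)² × 128 = 791.4, so 792. This matches exactly.
- Drop-out: 792 / 0.8 = 990 per group and 1584 / 0.8 = 1980 in total. These also match.

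**Step 2: try other readings of the same inputs.**

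| Reading | n per arm |
|---|---|
| Non-inferiority, one-sided 2.5%: (1.9600 + 0.8416)² × 128 = 1004.7 | 1005 |
| Equivalence, two one-sided 5% tests: (1.6449 + 1.2816)² × 128 = 1096.2 | 1097 |
| Superiority, 20% v 15%, one-sided 5% | 714 (753 with continuity correction) |
| Superiority, 20% v 15%, two-sided 5% | 906 |
| Superiority, 20% v 25%, one-sided / two-sided 5% | 862 / 1094 |

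The superiority rows use n = [z_α √(2p̄(1−p̄)) + 0.8416 √(p₁(1−p₁) + p₂(1−p₂))]² / 0.05², with p̄ the mean of the two proportions and z_α = 1.6449 (one-sided) or 1.9600 (two-sided). None of these gives 792. The calculation is therefore a one-sided 5% non-inferiority test.

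**Step 3: power under each decision interval.** Power = Φ(0.05/SE − z₁₋α), with SE = √(0.32/n).

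| n per arm | SE | 0.05/SE | Lower limit of 90% CI (z = 1.645) | Lower limit of 95% CI (z = 1.960) |
|---|---|---|---|---|
| 792 | 0.0201 | 2.4875 | Φ(0.843) = 80.0% | Φ(0.528) = 70.1% |
| 990 | 0.0180 | 2.781 | Φ(1.136) = 87.2% | Φ(0.821) = 79.4% |

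A simulation of 400,000 trials at 792 per arm with Wald limits gave 80.0% and 70.0%.

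**Step 4: size needed for 80% power on the 95% CI.** 1005 evaluable per arm, or 1005 / 0.8 = 1256.25, so 1257 per arm and 2514 in total after drop-out, against the planned 1980.

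**Step 5: results on which the choice matters.** With 792 per arm and SE 0.0201, the observed difference (IG minus CG) must exceed:

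- on the 90% CI: −0.05 + 1.645 × 0.0201 = −0.017;
- on the 95% CI: −0.05 + 1.960 × 0.0201 = −0.011.

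An observed difference between about −1.7 and −1.1 percentage points is non-inferior on the first and not on the second.

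**The case against.** The strongest reply is that nothing in the article is miscalculated and that no contradiction has been shown. Every figure in the sample size section reproduces. The hypothesis there is directional and labelled non-inferiority, so a single alpha of 0.05 is naturally read as one-sided, and the 792 bears this out. The sentence on 95% intervals is a general statement about presentation. It covers all models, including regressions and secondary endpoints, and does not say that the interval is two-sided or that it decides non-inferiority. Testing at one-sided 5% while showing 95% intervals is not inconsistent, and showing an interval does not change a test's power. The scale is also open: odds ratios are mentioned as one example for binary outcomes, whereas the power above is for a risk difference. Finally, the article is condensed, and a full protocol or SAP may name the decision interval.

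Most of this stands, and it limits the point. A reader might infer that the trial simply has 70% power, or that the sample size is wrong. The documents support neither. The 70% depends on a decision rule that the article does not state, and a one-sided 95% bound would restore 80%. Nor can it be said that the choice is open in the full documents, which are not shown.

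What remains is narrower. The article itself states a sample size and a confidence level, and on the ordinary reading of a 95% interval the two do not match. The one-sided level has to be recovered by reverse calculation, and the difference-test wording points the other way. An SAP could settle the rule, but the two published statements would still need reconciling.

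**Conclusion.** The point holds as a conditional one. The calculation of 792 per group is correct for a one-sided 5% test. The defect is its unreconciled pairing with a 95% interval, given that the sidedness of alpha is not stated. If non-inferiority is judged on the lower limit of a two-sided 95% CI, the stated 80% power becomes about 70% with 792 evaluable per arm. It becomes about 79% if all 990 per arm yield an outcome, so even with no losses it falls just short.

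These figures assume a true proportion of 20% in both arms, a risk-difference analysis with normal-approximation limits, and the conventional two-sided meaning of a 95% CI. The intention-to-treat statement, which includes all consenting participants, favours the upper end only in so far as outcomes are actually obtained; the plan itself allows for 20% drop-out.

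A one-sided 5% test is not wrong in itself. The matter still deserves correction because it governs how the primary conclusion is reached.

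**What to change.** Reconcile the sample size and statistical analyses sections before the data are seen, by one of two routes:

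1. State that non-inferiority is judged on the lower limit of the two-sided 95% CI for the risk difference against −0.05, and restate the power as 70% with 792 evaluable per arm, rising to 79% if all 990 contribute.
2. State that the primary test is one-sided at 5%, that the decision interval is the two-sided 90% CI (equivalently a one-sided 95% lower bound), and that the two-sided 95% CI is descriptive. The 792 and the 80% then stand.

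Either route takes a sentence or two and no extra patients. The first costs a less favourable stated power. The second costs an openly declared one-sided error rate of 5%. If a full protocol or SAP already names the decision interval, the article's text should be brought into line with it.

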## Discussion

The SALUS study is the first randomized, controlled prospective clinical trial to investigate the effectiveness of self-tonometry. The healthcare situation of glaucoma patients could be improved by the measuring of IOP over several days, especially in rural, structurally disadvantaged areas and those with fewer specialist health services.

In this study, patient-input is integrated into the diagnosis and treatment plan. It gives patients comprehensive insights into the course of their disease and promotes compliance. If self-tonometry is established in regular patient care as a result of SALUS, this could reduce the need for inpatient hospitalization. On the one hand, this would free up capacity in hospitals, and on the other hand, it would provide more comfort for patients, i.e., bring benefits without requiring extra effort or absence from work. The fact that patients could then remain in their accustomed domestic environment and daily routine is expected to improve their quality of life. They may save travel costs and would not be unnecessarily exposed to the risk of infection, especially in times of a pandemic. The taking of IOP measurements at a series of times predefined by the study will enable therapy to be optimally adjusted, and complications arising from delayed adjustments to therapy or more complex operations could possibly be avoided. The long-term benefit could be less blindness due to glaucoma. The telemedical focus could significantly improve healthcare by making medical services available independent of time and space. Telemedical networking via the cross-institutional ECF could optimize collaboration between the areas of healthcare provision and service providers. The ophthalmologist could rely on the support of continuously improving, self-learning algorithms in the evaluation of findings and therapy decisions, thus optimizing treatment strategies. Through digital networking, repeat medical examinations could be avoided when treatment of a patient takes place in another treatment center. The local ophthalmologists will be professionally supervised by a glaucoma expert and a senior resident and have the opportunity to base their treatment on an improved database.

Healthcare costs could be reduced by saving hospital resources. Once incorporated into standard care, economies of scale could lower prices further. Moreover, the fixed and implementation costs could be spread over a greater number of patients.

In summary, the SALUS study could be of great benefit to all parties involved, i.e., hospitals, patients, and also local ophthalmologists. In a further step, long-term comparative controls are necessary to assess the progression of glaucoma and further evaluate the reliability of self-tonometry. The focus on telemedicine is forward-looking and in line with current healthcare trends.

